## 2. Methods

### 2.1. Research Design

A cross-sectional quasi-experimental research design with retrospective data collection comparing the intervention group to the control group will be used. Because of the cross-sectional data collection, a randomised control trial is not an option and, therefore, propensity score matching will be used to improve causal inference in this experimental design, as has been used in other similar impact study settings [28,29,30]. PSM will match each treated unit with a nontreated unit of similar characteristics using propensity scores generated from chosen covariates. The preferred characteristics for matching so as to reduce bias and improve precision within the model in this study are education level, birth parity, income, and age of the participants [31]. 

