### 2.4. Study Population

The study population/sampling frame is composed of respondents at the household level who will be selected from two subcounties, one with mothers who have given birth between 2 and 12 months of age and who participated in the ttC model sessions (with 876 mothers in the treatment group forming part of the sampling frame), or mothers whose access to ttC sessions was limited to the other subcounty of interest (with 1355 mothers in the control group also forming part of the sampling frame). Thus, the total sampling frame/study population will have 2231 mothers from which the sample will be drawn. The mothers will be recruited from the CHW registers that show that they should have attended counselling sessions during their pregnancy. Inclusion criteria are that the mother had a baby between 2 and 12 months. All other mothers are excluded.

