### 2.8. Sampling Procedure

To reach the above calculated sample size, a three-stage sampling procedure will be used. First, a simple random sampling within Oyam district will be conducted to select one subcounty where the treatment (ttC implementation) was applied (Aber subcounty) and another where it was not (Otwal subcounty). This random selection ensured that both the intervention and the non-intervention areas were chosen in an unbiased manner.

In the second stage, stratified sampling will be done within the two subcounties to provide the sampling unit, being women of reproductive age (between 18 and 49 years) who have given birth to babies between 2 and 12 months of age. For internal homogeneity within each subcounty, two strata will be formed, one from each subcounty. A total of 930 mothers will be sampled from the 2231 eligible mothers (465 from the 876 available in the intervention subcounty and 465 from the 1355 available in the control subcounty) as per the sample size calculation above. 

Finally, in the third stage, a systematic sampling method will be applied to randomly select the 930 mothers from an alphabetically compiled list of eligible mothers. A random starting point and a fixed interval will be applied to select participants 465 participants from each subcounty. This process ensures an equal and unbiased representative sample for later generalisation of findings to other similar settings. The flow of this sampling process is shown in Figure 2 below.

By justifying and implementing this comprehensive sampling methodology, the study will aim to enhance the reliability and validity of the research findings.

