### 2.10. Data Analysis

After the data have been cleaned, they will be exported to STATA for analysis and Excel for better visualization. Descriptive and summary statistics will be drawn using the frequencies, measures of central tendency, and dispersion with proportions to provide a descriptive analysis of the context.

There will be cross tabulation of the chosen covariates (education level, birth parity, income, and age) with the intervention (ttC) to obtain their frequency distribution among the treatment and control arms together with the p-values. A logistic regression of the intervention and the covariates will be used to generate the propensity scores. A caliper width at the 20% of the standard deviation will be used for matching participants using the greedy nearest neighbor method in order to get the average treatment effects and the impact of the ttC intervention on the outcomes ANC, PoD, and PNC [40,41].

**
Sensitivity Analysis
**

Sensitivity analysis will be performed using the Rosenbaum bounds to test the conditional on the unobserved variables, and that the study is free from hidden bias [42]. This will use the rbounds commands in STATA version 14 ranging from 1 to 1.5 with an increment of 0.05. The gamma value will show whether hidden bias is present, as well as the robustness of the results to this potential hidden bias [43]. The sensitivity analysis results for the outcomes will demonstrate whether the treatment effects remain significant and robust to unobserved confounding, even in the presence of hidden bias. This should be across different gamma levels and confidence intervals to ensure the reliability and validity of treatment effects, therefore indicating stability [42,43].

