11th visit at 18 months of life (PNC)	Giving three to four meals to the child a day, child sleeping under a mosquito bed net.

Note: CHW = community health worker, ANC = antenatal care, HIV = human immunodeficiency virus, AIDS = acquired immunodeficiency syndrome, STIs = sexually transmitted infections, PoD = advised place of delivery, PNC = early postnatal care, ttC = timed and targeted counselling.

**Table 2 mps-07-00098-t002:** Study variables and their definitions.

Variable	Definition of Variable	Answering Scale
Intervention Variable		
ttC	This is a behavioural change approach implemented through CHWs to pregnancy households with a wide range of life-saving health practices through appropriately timed messages delivered using interactive storytelling to improve maternal health service utilisation. Mothers will be asked whether they received ttC from a CHW during their pregnancy.	1 = Yes 0 = No
Outcome Variables		
ANC	This is defined as visits to skilled health personnel during pregnancy. Mothers will be asked whether they attended any ANC visits during pregnancy.	1 = Yes 0 = No
PoD	This refers to the advised place of delivery, in a health facility. Mothers will be asked where they gave birth, with answering options including private health facilities, government health facilities, traditional birth attendant’s homes, or their own homes.	1 = Yes 0 = No
PNC	This refers to the care given mothers immediately after birth. This includes at least one PNC visit within the first 6 weeks after delivery. Mothers will be asked whether they visited a health facility for PNC after delivery.	1 = Yes 0 = No
Independent Variables		
Predisposing Factors		
Age	Mothers will be asked for their age at their last birthday.	1 = <20 2 = 21–25 3 = 26–30 4 = 31–35 5 = 36–40 6 = >40
Education level	Mothers will be asked for the highest level of school ever attended.	1. Preschool 2. Primary 3. O Level 4. A level 5. Tertiary 6. University 7. Non
Parity	Mothers will be asked how many births they have had in their lifetime, including the most recent one.	
Marital status	Mothers will be asked for their current marital status.	1. Widowed 2. Married or living together 3. Divorced or separated 4. Never married or never living together
Enabling Factors		
Income level	This refers to the income of the household. Mothers will be asked, on average, what is their approximate maximum monthly.	1. <200,000 2. >200,000–<500,000 3. >500,000–<1,000,000 4. >1,000,000–<2,000,000

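### Baby's age at interview governs recall length for the exposure and all three outcomes, and defines eligibility, but is neither a listed study variable nor a matching covariate

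*Protocol article*

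**What the plan says.** **Eligibility.** Section 2.4 states "Inclusion criteria are that the mother had a baby between 2 and 12 months". Section 2.8 repeats the window for women "who have given birth to babies between 2 and 12 months of age". The rule cannot be applied without establishing the baby's age for each mother.

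**Data collection.** Section 2.1 describes the study as follows: "A cross-sectional quasi-experimental research design with retrospective data collection comparing the intervention group to the control group will be used". Exposure is a yes/no item in Table 2: "Mothers will be asked whether they received ttC from a CHW during their pregnancy". The antenatal, place-of-delivery and postnatal outcomes are also the mother's answers. Table 2 defines the postnatal outcome by a visit in the first six weeks, but the question it describes only asks about attending a facility for postnatal care following the birth, with no time limit.

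**Covariates.** Section 2.1 says the preferred matching characteristics "are education level, birth parity, income, and age of the participants". Section 2.10 plans "cross tabulation of the chosen covariates (education level, birth parity, income, and age) with the intervention (ttC"), and then: "A logistic regression of the intervention and the covariates will be used to generate the propensity scores". The age item in Table 2 is the mother's age at her last birthday. Table 2 has no baby's age, date of birth or interview date.

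**Stated mitigation.** The limitations section accepts that self-report may bias answers and offers a confidentiality assurance. It does not mention length of recall.

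**The concern.** Time since birth varies between mothers by up to 12 - 2 = 10 months. It sets the recall length for six Table 2 items: ttC, antenatal care, place of delivery, postnatal care, partner accompaniment to antenatal visits, and psychological problems in pregnancy.

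It can enter the treatment comparison in three ways.

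1. **Recalled exposure.** If some mothers forget having had ttC as months pass, those with older babies drift into the No group. The same mothers may also report less care. Reported ttC and reported care are then associated through time since birth, with no true effect and no difference between Aber and Otwal in baby's age.
2. **Open-ended postnatal question.** As worded, a mother of a 12-month-old has had longer to reach a Yes than a mother of a 2-month-old. Table 1 labels contacts as late as 18 months as postnatal, so a late visit could be counted.
3. **Unequal baby ages.** If the compared groups differ in baby's age for any reason, both effects pass directly into the group difference.

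Matching on education, parity, income and mother's age does not address any of these. Selection does not balance baby's age either, since Section 2.8 samples systematically from an alphabetical list within each subcounty.

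**Working it through.** **The plan's own figure.** Section 2.7 gives 465 per group. With P1 = 71.5%, P2 = 81.5% and P = 76.5%:

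- n = 2 × (1.96 + 0.842)² × 0.765 × 0.235 / 0.10² = 282.3
- design effect: 282.3 × 1.5 = 423.4
- nonresponse: 423.4 × 1.10 = 465.8, in line with the stated 465

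This figure is not in dispute. It supplies the planned effect (10 points) and the effective size (about 282 per group) used below.

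**Case A: same age mix in both subcounties, groups defined by recalled ttC.** Assumptions, none from the documents:

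- baby's age A is uniform on 2-12 months, so its mean is 7 and its variance 10²/12 = 8.33
- half of mothers are truly exposed, independently of A, and unexposed mothers never report ttC
- the probability of reporting true ttC is 1 - d·A, with d = 1-3% per month
- the reported outcome falls by a proportion c = 1-2% per month from 76.5%
- ttC has no true effect

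Let p be the proportion reporting ttC, p = 0.5 × (1 - 7d). Mothers reporting ttC then have younger babies by

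gap = 0.5 × d × 8.33 / [p(1 - p)]

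- d = 1%: p = 0.465; gap = 0.0417 / 0.2488 = 0.17 months
- d = 3%: p = 0.395; gap = 0.125 / 0.2390 = 0.52 months

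The spurious difference is 0.765 × c × gap, in percentage points:

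| | c = 1% | c = 2% |
|---|---|---|
| d = 1% | 0.13 | 0.26 |
| d = 3% | 0.40 | 0.80 |

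The range is about 0.1-0.8 points, in favour of ttC.

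**Case B: baby's age differs between the groups.** Assume a proportional recall loss of 0.5-1.5% per month and a mean gap of 1-2 months.

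- At 76.5%: 0.765 × 0.005 × 1 = 0.4 points, up to 0.765 × 0.015 × 2 = 2.3 points
- At the 22.5% postnatal attendance quoted in the Introduction: 0.225 × 0.005 × 1 = 0.1 points, up to 0.225 × 0.015 × 2 = 0.7 points

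The direction depends on which group has the older babies.

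**Scale.** With 282 effective mothers per group, the standard error of the difference is √(2 × 0.765 × 0.235 / 282) = 3.6 points. With no true effect, the two-sided 5% test rejects 5.9% of the time at a bias of 1 point and 8.7% at 2 points.

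**Postnatal wording.** The documents give no figure from which to size this. Its direction is opposite to forgetting, because a longer time since birth raises the chance of a Yes. The net effect on that outcome therefore cannot be signed in advance.

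**The case against.** The strongest reply is that no imbalance is shown. Both subcounties use the same 2-12 month window. A reader might infer that their age mixes differ because Aber's registers are reviewed monthly under ttC while Otwal's are ordinary community health worker registers. The documents do not support that inference: the control-arm description says those registers are also updated and reported to district officials, and nothing indicates that register practice shifts baby's age within the window. Case B is therefore conditional.

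If the groups were defined by subcounty of residence instead of the mother's answer, Case A would disappear. Section 2.9 and Table 2, however, define the ttC variable by that answer, and Section 2.10 models the intervention variable.

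The questions are also coarse. Forgetting where one gave birth within a year is unlikely, so the assumed losses may be high for place of delivery. That stands, and it is a reason to treat the range as an illustration.

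Finally, Section 2.1 calls the four covariates preferred, the Abstract promises adjusted odds ratios without an adjustment set, and the questionnaire is not shown, so baby's age may well be collected. This is fair. The point is only that the article names its covariate set in two places and leaves out a variable it must already know. The six-week postnatal window is complete for every eligible mother, so there is no truncation of that outcome as defined. The issue is the unlimited wording of the question.

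**Conclusion.** The point holds in a limited form. Baby's age determines eligibility and recall length, is absent from Table 2 and from the named matching covariates, and can connect recalled ttC to reported outcomes. With equal age mixes the spurious difference is about 0.1-0.8 points on assumed recall losses. That is at most 8% of the planned 10-point effect and under a quarter of its standard error. It grows only if baby's age differs between the compared groups, and the documents do not show that it does.

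Two stronger readings should be resisted. One is that every self-reported answer is affected: education, current marital status, income, current chronic illness and mother's age are not recalled pregnancy events. The other is that adjustment would remove recall bias: it acts only on the part carried by baby's age. This is a worthwhile, low-cost correction. It is not evidence that the planned comparison is invalid.

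**What to change.** 1. Add baby's age in months at interview to Table 2, derived from date of birth and interview date.
2. Tabulate it by comparison group with the other covariates in Section 2.10.
3. Include it in the propensity score and in the post-matching outcome model behind the adjusted odds ratios.
4. State that this does not correct misclassified ttC, or recall that differs between groups at the same baby's age.

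The cost is one value already needed for screening and one extra model term. A few more mothers may fall outside the caliper. The sample size does not change.

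Repeating the analysis in mothers of babies aged 2-6 months is optional and should be labelled descriptive. If ages are uniform, (6 - 2)/(12 - 2) = 40% remain: about 0.40 × 423 = 169 respondents per group, or 169/1.5 = 113 after the design effect. The standard error is then √(2 × 0.765 × 0.235 / 113) = 5.6 points and power for a 10-point difference is about 43%. A non-significant result there would say little about recall.

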### 2.5. Study Instruments

This study will use a cross-sectional primary data source. Structured household questionnaires will be administered to the study participants by the research assistants to gather quantitative data. The questionnaire includes different data types, such as categorical, numerical, and scale options, to facilitate the quantification of information. For validity and reliability, the questionnaire will have embedded skips and rules to ease data collection and perform real-time data cleaning. The study tools/instruments to be used will also include the village health team (CHWs) household registers that register all the mothers at the household level and the ttC register that includes the targeted sessions and number of visits. These will provide the contact and location from which participants will be sampled and the data collected retrospectively.

Tools will be uploaded to Kobo Kollect, a data collection application that will be loaded on phone devices and administered. The Kobo loaded questionnaire will also have mandatory questions marked for emphasis and will have an embedded translation into the local language to ease data collection. A field pretest of the structured questionnaire will be performed before the final roll out.

### 2.6. Data Management

To ensure the integrity and accuracy of the collected data, a robust data management strategy will be implemented. A team of 25 research assistants will be trained and given pre- and post-training tests to test their knowledge with regard to the topic of study and data collection and management processes. The data will be checked for errors at the end of every day, and the research assistant team will meet daily after fieldwork to synchronize their data to a secure server to not only act as a backup, but also to allow the principal investigator to check for validity and accuracy of the tools using the GPS on the Kobo tools loaded on the phones and the time stamps on the tools showing the start and end time for each tool. There will also be ad hoc checks in the field to see that the data are not being manipulated into the system, but are actual data. The data collectors will also be given a unique identifier to enhance the traceability of each tool to individual entrants. Inaccurate information will therefore be easily traced to the research assistant who submitted it to the system, the records will be deleted, and the researcher will stop contributing to the data collection.

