### Conceptual Framework

The conceptual framework for this study is based on an adapted Andersen’s Behavioural Model (shown in Figure 1). It shows how maternal health behaviours are influenced by ttC in the presence of various factors proposed by Andersen’s model [25,26]. According to Andersen’s model, predisposing, enabling, and need-based factors affect maternal healthcare utilization [27]. In the current study, predisposing factors include social and demographic factors such as the mother’s age, education level, parity, and marital status. The enabling factors include income level of the household and male involvement in the pregnancy journey. The need-based factors are the presence of chronic illnesses, and psychological issues of the mother. While of importance to the study is the impact of ttC on maternal health behaviours, Andersen’s model helps us to account for how predisposing factors, enabling factors, and need-based factors shape healthcare utilisation. Secondarily, it contributes to understanding the contextual factors influencing maternal health outcomes, which supports efforts to address healthcare access inequality and inform policy development for more equitable access to care [25,26]. 

In this study, we shall incorporate Andersen’s model in investigating the impact of ttC (as an intervention) on ANC utilisation, PoD, and PNC. The ttC is hypothesised to influence maternal healthcare utilisation across the above three aspects by improving mothers’ knowledge on the benefits of fast and sufficient ANC visits, thus improving their attitudes towards ANC. ttC is also hypothesized to improve male-involvement, as well as enhancing the mother’s awareness of their health status and history, thereby affecting PoD and creating need for PNC.

**
General Objective
**

The main objective of this study will be to assess the impact of ttC on the maternal health continuum of care outcomes in Northern Uganda.

**
Specific Objectives
**

To investigate the impact of ttC on ANC utilisation among pregnant mothers.To evaluate the impact of ttC on the advised place of delivery among pregnant women.To assess the impact of ttC on PNC utilisation among mothers.

**
Hypotheses
**

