### 2.2. Research Area

The study area will be the northern region of Uganda, specifically the Oyam district, which was selected because ttC is implemented in the Aber subcounty of the district. Northern Uganda in particular is an important region for studying maternal health due to its high poverty rates [32], cultural diversity, limited healthcare access, poor health outcomes, and the presence of conflict-affected individuals [33].

Taking the Oyam district as the sampling frame, two subcounties, Aber and Otwal, are chosen for reaching out to mothers who would have given birth within the past 2–12 months. Aber is the treatment subcounty, and Otwal is the control subcounty because ttC is implemented in the former, but not in the latter. However, the two subcounties of Aber and Otwal were chosen because they are located within the same district and therefore have similar health challenges, such as limited health care access and similar poverty situations in the conflict-affected region [33]. Approximately 18.3% of the population in Aber and 22.3% of the population in Otwal aged 10–19 years have ever been married [34]. Furthermore, in 2021, these two subcounties, among others in Oyam district, had one of the highest teenage pregnancy rates in Uganda [35,36]. Factors mentioned by these new young mothers for the high rate of teenage pregnancy include a lack of knowledge of the ovulation period, inadequate sex education, and social norms that prevent parents from talking to their children about sex education [36]. Significantly, both subcounties are chosen because they do not share borders with each other; thus, limited spillovers are expected from the treatment subcounty to the control subcounty.

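### Distance to a health facility is absent from the propensity model, although the outcomes depend on reaching a facility and the interview GPS could supply it

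*Protocol article*

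**What the plan says.** All references are to the protocol article.

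- **Matching set.** Section 2.1 says the preferred matching characteristics "are education level, birth parity, income, and age of the participants". Section 2.10 repeats the set, planning "cross tabulation of the chosen covariates (education level, birth parity, income, and age) with the intervention (ttC)" and then a logistic regression to generate the scores.
- **Framework.** The Conceptual Framework states: "The enabling factors include income level of the household and male involvement in the pregnancy journey". Neither it nor Table 2 lists distance, travel time or any other measure of access.
- **Outcomes.** Table 2 says of place of delivery: "This refers to the advised place of delivery, in a health facility". It asks about postnatal care as a visit to a health facility. Antenatal care is defined there as visits to skilled personnel; the Introduction puts that contact at health facilities.
- **Comparability.** Section 2.2 justifies the choice of Aber and Otwal because they are "located within the same district and therefore have similar health challenges, such as limited health care access", and adds that they share no border.
- **Data in hand.** Section 2.5 states: "Structured household questionnaires will be administered to the study participants by the research assistants to gather quantitative data". Section 2.6 has the principal investigator "check for validity and accuracy of the tools using the GPS on the Kobo tools loaded on the phones and the time stamps". No other use of GPS is stated.
- **Unmeasured confounders.** The limitations section leaves these to sensitivity analysis. Section 2.10 specifies Rosenbaum bounds with gamma from 1 to 1.5.

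**The concern.** A mother's distance from a facility plausibly affects whether she delivers there or returns for postnatal care, whatever counselling she received. The protocol itself describes the region by limited access to care. Treatment follows subcounty, one treated and one control, so a difference in typical distance between the two is a difference between the arms. Education, parity, income and age are personal characteristics and need not remove it.

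Section 2.2 rests comparability on two similarities, poverty and access. Poverty is at least approached through household income, which is tabulated by arm and matched on. Access is neither tabulated nor matched on. Being in the same district does not make two non-adjacent subcounties equally close to their facilities.

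Unlike most differences between the subcounties, distance varies from mother to mother within each one. It can therefore be balanced, as far as the two distributions overlap, even with a single subcounty per arm.

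**Working it through.** **1. Reproduce the planned sample size.** Inputs from section 2.7: P1 = 71.5%, P2 = 81.5%, P = 76.5%, Z values 1.96 and 0.842, design effect 1.5, nonresponse 10%.

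n = 2 × (1.96 + 0.842)² × 0.765 × 0.235 / 0.10² = 282.3

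282.3 × 1.5 = 423.4; × 1.10 = 465.8. Carrying 282 forward gives 465.3. The stated 465 per group reproduces.

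**2. Standard error of the facility-delivery difference.** With 423 responders per group and design effect 1.5:

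SE = √(1.5 × 2 × 0.765 × 0.235 / 423) = 0.0357, or 3.57 points. This agrees with 10 / 2.802 = 3.57.

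**3. Bias from distance.** The documents give no distances, facility locations or gradient of attendance with distance. Assumed: attendance falls 2 to 4 points per extra kilometre, and the subcounty means differ by 0 to 1 km. Bias = slope × difference in mean distance.

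**4. If Aber is closer and ttC has no effect.** Two-sided 5% test, with Φ the standard normal distribution function:

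P(reject) = 1 − Φ(1.96 − bias/SE) + Φ(−1.96 − bias/SE)

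| Difference in mean distance | Bias (points) | Share of 10 points | False-positive chance |
|---|---|---|---|
| 0 km | 0 | 0% | 5% |
| 0.25 km | 0.5 to 1 | 5% to 10% | 5.2% to 5.9% |
| 0.5 km | 1 to 2 | 10% to 20% | 5.9% to 8.7% |
| 1 km | 2 to 4 | 20% to 40% | 8.7% to 20.2% |

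**5. If Otwal is closer and the true effect is 10 points.** The bias is subtracted. Power ≈ Φ((10 − bias)/3.57 − 1.96):

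- bias 0: Φ(2.80 − 1.96) = 80%
- bias 2: Φ(2.24 − 1.96) = 61%
- bias 4: Φ(1.68 − 1.96) = 39%

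**6. Would the planned bounds cover it?** Suppose, again by assumption, that 50% of control mothers live far from a facility. If 40% of treated mothers do, the odds ratio is (0.5/0.5)/(0.4/0.6) = 1.5, the top of the planned gamma range. If 30% do, it is (0.5/0.5)/(0.3/0.7) = 2.33, outside it. If living far lowers facility delivery by 5, 10 or 20 points, the 30% versus 50% split gives a bias of 0.20 × 5, 10 or 20 = 1, 2 or 4 points, the same order as in step 4 by a different route.

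**The case against.** **The sentence in section 2.6 contains no error.** It describes quality control and excludes no other use of GPS. A reader might infer that the plan confines GPS to policing interviewers; the text supports only that no other use is stated. This stands. The weakness lies in the covariate set fixed in sections 2.1 and 2.10.

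**Access is not the only testable part of the comparability argument.** Section 2.2 also claims "similar health challenges, such as limited health care access and similar poverty situations in the conflict-affected region", and household income is collected, tabulated by arm and matched on. It would be wrong to say that access alone can be checked with the study's own data. Access is the half that the plan leaves unchecked.

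**The similarity claim carries a citation.** That source is not available here, so the claim is not bare. But the stated reasoning is the shared district, and a general description of the region would not show that these mothers are balanced on distance.

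**Confounding is acknowledged.** The limitations section and the Rosenbaum bounds address it in general terms. Bounds describe robustness to what was not measured; they do not replace adjustment for something that can be measured, and gamma stops at 1.5. The Abstract also mentions adjusted odds ratios after matching, but Table 2 offers no access variable to adjust for.

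**An article condenses.** The questionnaire is not shown and might contain a travel item. Table 2 defines the study variables and has none, and the matching set is stated twice, so this is a stated choice and not a detail left out.

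**The measure is imperfect.** Interviews take place 2 to 12 months after birth, so the position may not be the home during pregnancy. That the point lies at the home is itself inferred from the household questionnaire. The nearest facility may not be the one used. These points weaken the covariate without removing its value.

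**Conclusion.** The point holds as a worthwhile improvement to the covariate set. The model omits a measurable determinant of the outcomes that can differ between the two subcounties, while similar access is inferred and not shown.

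Under the assumed slope of 2 to 4 points per kilometre and a mean difference of 0 to 1 km, the bias is 0 to 4 points in either direction. For facility delivery that means a false-positive chance between 5% and about 20% if Aber is closer, or power falling from 80% to as low as 39% for a true 10-point effect if Otwal is closer. These figures illustrate; they are not estimates. They assume that the four matched covariates remove none of the distance effect and that the planned number of responders is analysed. They should not be carried over to antenatal care, which is asked as any attendance, or to postnatal care, since each has its own level and possibly its own gradient.

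Two stronger readings are tempting. One is that ttC's effect will be overstated; the documents give no distances, so neither sign nor size can be claimed, and zero is possible. The other is that adding distance makes the arms comparable; with one subcounty per arm, facility quality and every other difference between the subcounties remain confounded with treatment.

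**What to change.** 1. Derive, for each mother, the distance from the household GPS point to the nearest facility offering the relevant services (antenatal care, delivery, postnatal care), and add it to Table 2 as an enabling factor.
2. In section 2.2, replace the inference of similar access with a table of this distance by subcounty.
3. In section 2.10, add distance to the propensity model and check overlap. If overlap is poor, adjust for distance after matching instead, and say so in the report.
4. Ask whether the mother lived at the same place during pregnancy, or list this as a limitation.
5. State in the limitations that other subcounty-level differences remain confounded with treatment.

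Reporting the effect by distance band is optional: the sample was sized for one overall contrast.

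**Cost.** A list of facility coordinates with the services offered, which the documents do not mention and which must be obtained; one derived variable; and GPS kept in the secured analysis file, with the confidentiality care that implies. Some pairs may be lost to the caliper, with some loss of precision. The recruitment target of 465 per group need not change.
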